### **Statistical methods**

#### ***Data preparation***

### *Missing covariate data*

Covariates at a given time  $t$  will be defined by the status at the most recent assessment available prior to that screening date. If the covariate is not available in a look back up to a max of two years prior to that screening date it should be declared as missing.

Covariates missing within this time horizon of patient entry date in more than 40% of participants will be excluded. Where the missingness is  $< 40\%$  multiple imputation (see statistical methods section) will be used to assign a value based on other variables observed for the patient as well as surrounding values of that particular variable.

Covariate terms will also be set up for age x covariate and sex x covariate interactions for each covariate.

“MI” R package will be used for imputation. 10 iterations with 2 chains will be used, with seed = 1986. No consideration of event status is made in the imputation.

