### **Initial tabulations**

For each continuous covariate being considered :

- Summarise its distribution as mean median sd iqr and range and plot its distribution (density or histogram) plot
- Tabulate the frequency of all categorical variables

Events:

- Show the number (%) and event rate of incident events during follow up By AGE and SEX and diabetes type
- By Sex strata and for broad age bands and all ages combined show the age standardised event rate for each of the event of interest standardised to the 2013 European Standard Population

Then with any referable retinopathy as the event of interest :

- Summarise the distribution of follow up time range of person entry and exit dates
- Summarise the distribution of covariates at baseline by subsequent event status

- In the same table show the p value and the beta regression coefficient for the current age - sex -and diabetes duration -adjusted associations of all variables with the outcome

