### a. Poisson regression

We will use Poisson regression model with backward elimination but we may use a different link function to deal with the interval censoring - In addition we will evaluate the use of non-parametric methods for interval-censored survival analysis in place of the interval regression models.

All model fitting will be done on 70% of the data (selected randomly by patient, maintaining ratio of events), and the remaining 30% will be used for internal validation. We will randomly assign the individuals in the dataset into these two partitions.

We include current age, sex, and diabetes duration as our base set of covariates in our initial model and will then use backward elimination to drop variables from the model, using a reduction in AIC of  $< 2$  units as the selection/stopping criterion.

We will initially include a simple covariate of screening status at last screening as a covariate

We will then extend this to be a weighted score of all prior screenings weighted by how recent the measure is

The model will contain an offset term for the  $\log(\text{length of interval})$ .

We will also select across age and sex interaction terms for each covariate.

To be agreed : should we include any shrinkage/ penalizing?

*Assumption about linearity of effects of covariates :*

We will use backward elimination with multivariable fractional polynomials

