### b. Two-step analysis with multi-state modelling & survival analysis:

We will use hidden Markov models to model the DRS data. The advantages to this approach are that it allows us to model the risk for transition incorporating all available data on prior screening even though individuals have variable number of examinations at differing intervals. It also allows us to model grading misclassification as it separates the 'true but unseen grade' from the 'observed grade'. We will fit separate models by diabetes type and the models will be adjusted for age, sex and diabetes duration. As it is not feasible to extend the multi-state modelling approach to a more complex model that includes many clinical covariates we will "plug in" the risk score computed from the hidden Markov model into the fuller model that includes all available clinical covariates as described above.

**One-step survival analysis:** We will evaluate an alternative approach of not using the hidden Markov model but instead fitting separate models for individuals with 0, 1, 2 or more previous examinations. This is possible as we have a large dataset so that we will have an adequate sample size to learn a predictive model within each of these strata.

**Non-parametric methods:** We shall also evaluate non-parametric methods for interval-censored survival analysis. These kernel-based methods, which make predictions based on a function that evaluates the similarity between pairs of observations, generally outperform simple regression models for prediction though the predictions are not readily explainable.

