### Performance evaluation

The performance of the final model will then be reported from the test dataset.

Discrimination will be assessed using a C-statistic (area under the receiver operating characteristic [AUROC]). We will calculate the AUROC within age and sex strata and then take a weighted average of these to define the final AUROC.

Calibration will be summarized using a calibration plot, calibration slope, and Hosmer-Lemeshow test.

We will also report out the net reclassification indices and the IDI. However note that we consider the AUROC to be the most valid of these. Integrated Discrimination Index (IDI). The IDI =  $(IS_{new} - IS_{old}) - (IP_{new} - IP_{old})$  where IS is the integral of the sensitivity across all possible cut-off values for the new ( $IS_{new}$ ) and old models ( $IS_{old}$ ) and IP the corresponding integral of 1-specificity with the new model reflecting the model with added clinical covariates and the old model being based only on the DRS screening data. These metrics will allow us to assess how well these models improve prediction of risk for transition to referable eye disease.

In the test set we will compare the predictive performance of the prediction model with this hidden markov derived measure with the simpler indices of past screening results as described under a. above

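### The imputation setting gives only 2 chains of 10 iterations under one seed, with no number of completed data sets, pooling rule or convergence check, although covariates with up to 40% missing are kept

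*SAP*

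**What the plan says.** The SAP section *Missing covariate data* sets an exclusion limit: "Covariates missing within this time horizon of patient entry date in more than 40% of participants will be excluded". Below that limit, "multiple imputation (see statistical methods section) will be used to assign a value based on other variables observed for the patient", with surrounding values of the same variable also used. The MI "R package will be used for imputation", and the setting is "10 iterations with 2 chains will be used, with seed = 1986".

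That is all the plan says about the procedure's size. The pointer to a statistical methods section leads to no further text on imputation: neither the modelling sections nor *Performance evaluation* mentions it again. The number of completed data sets, the combination of results, a convergence check and a repeat under another seed are all unstated.

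The imputed covariates feed three planned outputs:

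- *Initial tabulations* will "show the p value and the beta regression coefficient" for every variable.
- *Poisson regression* "will then use backward elimination to drop variables from the model, using a reduction in AIC of" less than 2 units as the criterion, and also selects across age and sex interactions and fractional polynomials.
- *Utility assessment* sets individual screening intervals from predicted risk, with 1%, 2.5% and 3% as example thresholds.

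**The concern.** Multiple imputation represents the uncertainty about missing values through the spread between completed data sets. That spread must be estimated from the sets themselves. The only count the plan offers is two chains. If that count is also the number of completed data sets, the spread is estimated from one difference. If more sets are taken from the same two chains, their number is undefined in a pre-specified plan, and they still come from two short runs whose convergence no stated rule checks.

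With too few sets, standard errors and p values become erratic, and terms near the AIC cut-off may enter or leave according to the seed. A person whose covariate was imputed gets a predicted risk averaged over very few draws, and that risk may set a screening interval.

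**Working it through.** The SAP has no figure of its own to reproduce here. The check uses Rubin's rules.

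**Inputs.** From the SAP: 2 chains, and a 40% limit on missingness at entry. Assumed: m = 2 (one completed data set per chain), and a missing-information fraction λ = B/(W + B) of 0.1 to 0.4, where W is the within-imputation and B the between-imputation variance. The SAP reports no actual missingness. The value 0.4 is roughly what the limit would imply if the other variables said little about the missing value.

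**Between-imputation variance.** The estimate of B has m − 1 = 1 degree of freedom. As a multiple of its true value it follows a chi-square on 1 df. It is below one quarter 38% of the time and above double 16% of the time; its central 95% range is 0.001 to 5.02.

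**Pooled estimate.** Set W = 1, so B = λ/(1 − λ). Then:

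- relative efficiency = 1/(1 + λ/m)
- r = (1 + 1/m)B and total df = (m − 1)/[r/(1 + r)]²
- seed noise, as the SD of the pooled coefficient over seeds divided by its standard error (SE), = √(λ/m)

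Worked for λ = 0.4, m = 2: B = 0.4/0.6 = 0.667; r = 1.5 × 0.667 = 1.0; r/(1 + r) = 0.5; df = 1/0.25 = 4. Efficiency = 1/1.2 = 0.83. Seed noise = √0.2 = 0.45 SE. The 95% multiplier on 4 df is about 2.78, against 1.96. (Putting 0.4 straight into (m − 1)/λ² gives 6.25 df and a multiplier of 2.42. That omits the factor 1 + 1/m, which matters most when m is smallest.)

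| λ | m | Efficiency | Total df | Seed noise (SE) | CV of the SE |
|---|---|---|---|---|---|
| 0.1 | 2 | 0.95 | 49 | 0.22 | 9% |
| 0.2 | 2 | 0.91 | 13 | 0.32 | 17% |
| 0.4 | 2 | 0.83 | 4 | 0.45 | 30% |
| 0.4 | 20 | 0.98 | 112 | 0.14 | 7% |
| 0.4 | 40 | 0.99 | 237 | 0.10 | 5% |

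The last column was simulated by drawing B from its chi-square distribution.

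**Borderline selection.** The plan does not say how AIC is combined across sets, so selection was approximated by a pooled Wald chi-square above 2. For a term whose z is 1.25 times the cut-off, two seeds disagree about:

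- λ = 0.4: 41% of the time with m = 2, 5% with m = 20 and 0.4% with m = 40
- λ = 0.2: 32% with m = 2 and 0.2% with m = 20

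A term exactly on the cut-off flips half the time at any m. At 1.5 times the cut-off and λ = 0.4, the figures are 25% with m = 2 and essentially none with m = 20.

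**Individual risk, as an illustration.** Assume a log rate ratio of 0.3 per SD of the covariate and an imputation residual SD of 0.8. One draw adds 0.3 × 0.8 = 0.24 to the SD of the log risk. Averaging two draws leaves 0.24/√2 = 0.17, so a 2.5% risk ranges from about 2.1% to 3.0% at ±1 SD. Forty draws leave 0.24/√40 = 0.04.

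**The case against.** The strongest objection is that chains are not completed data sets. The SAP never says m = 2, so the firm defect is that the number and the combination rule are unstated. That stands, and every figure above for m = 2 is conditional on it. It does not rescue the setting: the plan supplies no other number, and two short runs remain the only independent source of imputations.

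Second, 40% is a limit on missingness, measured only at entry, and not the fraction of missing information. Using other variables and neighbouring values of the same variable should bring the fraction down. That also stands, which is why the range runs down to 0.1. There the loss is modest, and a common rule for a 5% CV of the standard error, m = 1 + 0.5(λ/0.05)², asks for only 3 sets. It asks for 9, 19 and 33 at 0.2, 0.3 and 0.4.

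Third, this is a prediction study. The p values sit in a descriptive table, AIC selection does not use pooled standard errors directly, and of the reclassification and discrimination measures the plan says "However note that we consider the AUROC to be the most valid of these". It also describes the data as large: "This is possible as we have a large dataset so that we will have an adequate sample size". A reader might infer that the results as a whole depend on the seed. The SAP does not support that: noise of at most about 0.45 SE is small in absolute terms when standard errors are small, so overall AUROC, calibration and strong predictors should move little. But sample size does not settle terms near the cut-off, and it does not shrink the noise in one person's imputed value.

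Two further inferences go too far. The 1 df belongs to the between-imputation variance, not to the pooled test. And nothing in the SAP shows that 10 iterations are too few: two chains can be compared with each other, but the plan states no check. Fixing a seed is good practice for reproducibility; the weakness is relying on one seed with so few runs.

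**Conclusion.** The point holds in a limited form. As written, the imputation rests on two short runs under one seed, and the plan does not say how many completed data sets follow or how they are combined. Under the assumption m = 2, efficiency is 0.83 to 0.95 and seed noise 0.45 to 0.22 SE as the missing-information fraction falls from 0.4 to 0.1. The consequences are confined to the tabulated p values, selection near the AIC cut-off, and risks for people with imputed covariates. The selection and individual-risk figures are illustrations that rest on the approximations stated with them. This is a worthwhile and inexpensive improvement; it does not show that the model's overall performance would be wrong.

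**What to change.** In *Missing covariate data*, replace the current setting with:

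- about 20 to 40 completed data sets, near the highest percentage missing among the retained covariates
- more than two chains, run until a named convergence check is met
- a rule for pooling coefficients and standard errors, and for averaging predicted risks across sets
- a rule for AIC-based elimination, interactions and fractional polynomials across sets, since pooling alone does not say which terms are kept
- a repeat of the imputation and model selection under a second seed, with any change in the selected terms reported

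The text is short. The real cost is computing time on a large longitudinal data set, chiefly from repeating model selection over many completed copies. No new data are needed.

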### *Event dates*

The date of the event will be taken as the date of screening on which referable retinopathy was detected. Each person time interval has a binary flag for whether an event occurred in a person-time interval.

We also have a censor date (which is the earliest of death/event/study end date/end of observability). If a person is censored and his event flag is 1, then that means he was censored because of the event. If at the person's last time-interval the event flag is 0, then he was censored for one of the other reasons (i.e. akin to a SURV object in R for Cox regression).

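### Event status is left out of all imputation, including in the 70% of patients used to fit the model, so coefficients of incompletely recorded covariates are biased toward zero

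*SAP*

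**What the plan says.** Under Missing covariate data, each screening row takes the latest earlier assessment of a covariate, and a value counts as missing when two years of look-back yield none. The exclusion rule is "Covariates missing within this time horizon of patient entry date in more than 40% of participants will be excluded". Below that ceiling, values are multiply imputed from the patient's other variables "as well as surrounding values of that particular variable". The settings are "10 iterations with 2 chains will be used, with seed = 1986", followed by "No consideration of event status is made in the imputation".

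Under a. Poisson regression, "All model fitting will be done on 70% of the data (selected randomly by patient, maintaining ratio of events"), with the remaining 30% kept for internal validation. The fitting method is "We will use Poisson regression model with backward elimination", using AIC. No section restricts the omission of event status to the validation patients, gives a reason for it, or plans a sensitivity analysis on it. The text refers to a statistical methods section for the imputation, but no further imputation detail appears there.

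**The concern.** Values drawn without the outcome carry information about the event only through the variables used to draw them. Where those leave part of the covariate unexplained, the unexplained part of each imputed value is noise with respect to the event. Fitting a rate model to a mixture of recorded and imputed values then dilutes the covariate's coefficient.

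Three things follow. Covariates with gaps get too little weight, while correlated, completely recorded covariates take up part of their effect. Weak main effects, and the age and sex interactions built from them, are more easily lost in backward elimination. The comparison under Performance evaluation between a model with clinical covariates and one based only on screening data leans against the clinical covariates. The Utility assessment assigns screening intervals by risk thresholds such as 1%, 2.5% or 3%, so patients with recorded values whose risks are pulled toward the average may be placed on the wrong side of a threshold.

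**Working it through.** The SAP states no coefficient or missingness figure, so there is nothing to reproduce. The check asks how large the dilution can be under the SAP's rule and whether adding the outcome removes it.

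**From the SAP:** covariates imputed up to 40% missing at patient entry (later rows have no cap); imputation from other variables and neighbouring values; Poisson model with a log interval-length offset. The outcome is available for imputation: "Each person time interval has a binary flag for whether an event occurred in a person-time interval".

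**Assumed, not in the SAP:** true log rate ratio 0.40 per SD; about 3% events per year; one complete covariate correlated 0.3 with the incomplete one; 10, 20 or 40% missing; a neighbouring value of the same variable with correlation r = 0, 0.5 or 0.8; missingness either completely at random (MCAR) or dependent on the complete covariate (MAR).

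**Formula (MCAR, linear approximation).** With missing share m, and R² the part of the covariate's residual variance explained by imputation predictors outside the outcome model (here r²):

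expected ratio to the true coefficient = 1 - m(1 - R²)

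At m = 0.40:
- r = 0: 1 - 0.40 × 1 = 0.60
- r = 0.5: 1 - 0.40 × 0.75 = 0.70
- r = 0.8: 1 - 0.40 × 0.36 = 0.856

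**Simulation.** 40,000 rows, 12 replicates and 5 imputations per scenario. Entries are the coefficient imputed without the outcome divided by the full-data coefficient, for r = 0 / 0.5 / 0.8. The standard error of the mean coefficient was 0.005 to 0.010.

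| Missing | Formula | Simulated, MCAR | Simulated, MAR |
|---|---|---|---|
| 10% | 0.900 / 0.925 / 0.964 | 0.890 / 0.932 / 0.957 | 0.867 / 0.892 / 0.956 |
| 20% | 0.800 / 0.850 / 0.928 | 0.789 / 0.841 / 0.931 | 0.739 / 0.802 / 0.912 |
| 40% | 0.600 / 0.700 / 0.856 | 0.595 / 0.706 / 0.845 | 0.547 / 0.645 / 0.837 |

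A further simulation gave ratios of about 0.89-0.95 at 10% missing and 0.62-0.83 at 40%.

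**With the outcome in the imputation model.** Adding the event flag and interval length brought the ratio to 0.98-1.04 in all 18 scenarios above, and to about 0.92-1.03 in the further simulation.

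**Absorption.** At 40% missing, MCAR, r = 0, the complete covariate's coefficient rose from 0.296 to 0.344 (0.344 / 0.296 = 1.16).

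**Predicted risk.** Simulations carried through to a test set imputed without the outcome used a baseline rate of 2% and a log rate ratio of 0.4 where settings are stated. Under the SAP's rule:
- The overall test calibration slope was about 0.98-1.06.
- AUROC differed from that under the fix by 0.004 or less.
- Among patients with the value recorded, the slope was at most 1.03 when prior screening status was a strong predictor (log rate ratio 0.8 per SD) and at most about 1.10 in a second set. A third set, MCAR with no informative neighbouring value, gave 1.07, 1.10 and 1.17 at 10, 20 and 40% missing. At 40%, the top risk decile of recorded patients in that set had a predicted rate of 4.8% against 5.2% observed.
- In that third set the overall slope was 1.02, 1.01 and 1.02, because imputed patients had slopes of 0.63, 0.66 and 0.81. The two groups offset each other, so the overall calibration plot and slope would not show the problem.

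**The case against.** The strongest defence is that the aim is prediction, not estimation. In use the outcome is unknown when gaps are filled, so imputing without it in development matches use. That is a sound reason to omit the outcome in the test set, and a reader should not infer that the omission is wrong there. It does not justify omission where coefficients are estimated: most of the planned predictors may be recorded for a given patient, and that patient's risk should rest on undiluted coefficients.

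A second defence is that the fix can worsen calibration. With corrected coefficients and one outcome-free draw per test patient, the slope fell to 0.93 in one simulation (against 0.99 under the SAP's rule) and as low as 0.90 in another. This holds for single draws only. Averaging predicted risk over several draws gave 0.98-1.02.

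Third, 40% is an exclusion ceiling and not an expected level, and the plan uses neighbouring values, which lessen the loss. Both points stand. They limit the size: the r = 0 figures are the unfavourable end, not the expected case. They do not remove the bias, since at r = 0.8 and 40% missing the ratio is still about 0.84. A value counts as missing only when the two-year look-back is empty, so the nearest earlier value is more than two years old.

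A reader might also infer from the two chains that only two completed data sets are planned. The SAP gives chains and iterations but not the number of completed data sets, so that inference is unsupported and forms no part of this point.

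**Conclusion.** The rule is wrong as written for the 70% development set. It biases the coefficients of incompletely recorded covariates toward zero, by about 5-15% at 10% missing and about 15-40% near the ceiling. The one simulated value beyond that range, 45%, needs 40% missing, MAR, and no informative neighbouring value. Correlated complete covariates absorb part of the effect, terms become more likely to be dropped by AIC, and the added value of clinical covariates is somewhat understated.

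A reader might infer that the screening tool would be badly calibrated or would discriminate poorly. The evidence does not support that: overall calibration and AUROC hardly change. Compression of risk in fully recorded patients is up to about 10%; the 1.17 slope arose only at 40% missing with no informative neighbouring value, which is less favourable than the SAP's procedure. Movement of patients across the risk thresholds was not computed.

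These sizes rest on assumed effect sizes, one incomplete covariate, and MCAR or MAR missingness. Several incomplete covariates together could enlarge them. The point should be fixed before the models are fitted, but it is not critical to the validity of the study.

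**What to change.** Replace the sentence on event status with separate rules for the two partitions:

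- **Development set (70%):** the imputation model includes the event flag and log interval length (or the cumulative hazard), along with the patient's other variables and neighbouring values.
- **Test set (30%):** missing values are imputed without the event flag, using an imputation model without the outcome estimated in the development data. Predicted risks are averaged over several imputations per patient, not taken from a single draw.

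Reporting the calibration slope separately for test patients with and without imputed values would show whether any compression remains. If the sponsor prefers to omit the outcome in development to mirror use, the SAP should say so and add a sensitivity analysis with the outcome included.

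The cost is SAP wording and computing time. Running selection, fractional polynomials and interactions across several completed data sets is a burden the SAP already takes on by choosing multiple imputation; adding the event flag does not create it.
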